## Abstract

**Background:**

Despite the high incidence and the economic impact of the common cold, there are still no effective therapeutic options available. Although traditional Chinese medicine (TCM) is widely used in China to treat the common cold, there is still a lack of high-quality clinical trials. This article sets forth the protocol for a high-quality trial of a new TCM drug, *Baoji Tablets*, which is designed to treat the common cold with summer-heat and dampness syndrome (CCSDS). The trial is evaluating both the efficacy and safety of *Baoji Tablets.*

**Methods/design:**

This study is designed as a multicenter, phase II, parallel-group, double-blind, double-dummy, randomized and placebo-controlled trial. A total of 288 patients will be recruited from four centers. The new tablets group are administered *Baoji Tablets* 0.9 g and dummy *Baoji Pills* 3.7 g. The old pills group are administered dummy *Baoji Tablets* 0.9 g and *Baoji Pills* 3.7 g. The placebo control group are administered dummy *Baoji Tablets* 0.9 g and dummy *Baoji Pills* 3.7 g. All drugs are taken three times daily for 3 days. The primary outcome is the duration of all symptoms. Secondary outcomes include the duration of primary and secondary symptoms, changes in primary and secondary symptom scores and cumulative symptom score at day 4, as well as an evaluation of treatment efficacy.

**Discussion:**

This is the first multicenter, double-blind, double-dummy, randomized and placebo-controlled trial designated to treat CCSDS in an adult population from China. It will establish the basis for a scientific and objective assessment of the efficacy and safety of *Baoji Tablets* for treating CCSDS, and provide evidence for a phase III clinical trial.

**Trial registration:**

This study is registered with the Chinese Clinical Trial Registry. The registration number is ChiCTR-TRC-13003197.

## Background

The common cold is the conventional term used to describe a mild, self-limited, viral, upper respiratory tract infection and it is the most prevalent disease experienced by humans [1]. Symptoms usually include a sore or scratchy throat, sneezing, coughing, hoarseness, runny nose, nasal obstruction and mild general symptoms like fever, headache, chills and not feeling well in general [2]. However, in clinical practice, symptoms caused by the common cold vary from person to person, and cold to cold. Well over 200 viruses are implicated in the cause of the common cold [3]. Among these pathogenic viruses, adenoviruses and enteroviruses can even cause diarrhea [4-6]. It has been reported that acute upper respiratory infection is the most common discharge diagnosis in emergency departments and the second most common diagnosis in physician offices [7,8]. In the United States, the costs associated with noninfluenza viral respiratory infections are estimated at 40 billion dollars each year, including indirect and direct costs [9]. Despite the high incidence and the economic impact of the common cold, no effective etiological treatment has been proven. Treatment thus mainly comprises symptomatic relief [10]. Although various treatments are used in clinical practice nowadays, few of them are supported by any solid evidence.

Dissatisfaction with conventional treatments offered by Western medicine has resulted in many patients seeking help from complementary and alternative medicine. Traditional Chinese medicine (TCM), a 5000-year-old ancient system of medicine, has been used to treat a wide range of diseases, including the common cold. The TCM treatment for common cold is based on the differentiation of symptoms and signs, such as fever, fatigue, headache, aversion to cold, nausea and vomiting, nasal discharge, stuffy nose, tongue proper, tongue coating and condition of pulse. With a totally different system of concepts and theories for etiology, TCM divides colds into three categories: wind-heat syndrome, wind-cold syndrome and summer-heat and dampness syndrome. Among them, the common cold with summer-heat and dampness syndrome (CCSDS) is most commonly seen in midsummer and it is primarily characterized by aversion to cold, fever, diarrhea, nausea and vomiting. According to the basic principles of TCM, CCSDS is treated by dispersing summer-heat and resolving dampness, as well as improving the spleen’s transportation function.

A new TCM drug, *Baoji Tablets*, is manufactured by Wanglaoji Pharmaceutical Co Ltd, Guangzhou, China. It is a new dosage form of *Baoji Pills*, which is an old and famous traditional Chinese preparation in the form of tiny round balls, 3 to 5 mm in diameter, used for treating CCSDS. This patented drug is made of active ingredients from the Chinese herbs listed in Table 1, which have all been approved by the China Food and Drug Administration (CFDA) [11]. Preclinical pharmacologic experiments showed that it can disperse summer-heat, resolve dampness and improve the spleen’s transportation function. Furthermore, no evidence of an adverse or toxic effect has been found in toxicological studies. The preclinical studies were completed by [name] and her research team from the new drug development research center of Guangzhou Traditional Chinese Medical University. Their studies have not yet been published.

**Table 1 T1:** **Standard formulation of ****
*Baoji Tablets*
**

**Pinyin name**	**Latin name**
Gouteng	*Ramulus uncariae cum uncis*
Juhua	*Flos chrysanthemi*
Jili	*Fructus tribuli*
Houpo	*Cortex magnoliae officinalis*
Cangzhu	*Rhizoma atractylodis*
Tianhuafen	*Radix trichosanthis*
Guanghuoxiang	*Herba pogostemonis*
Gegen	*Radix puerariae*
Huajuhong	*Exocarpium citri grandis*
Baizhi	*Radix angelicae dahuricae*
Yiyiren	*Semen coicis*
Daoya	*Fructus oryzae germinatus*
Bohe	*Herba menthae*
Fuling	*Poria*
Guangdongshenqu	*Massa medicata fermentata*

The objective of this well-designed randomized controlled trial is to evaluate the efficacy and safety of *Baoji Tablets* by comparing it with the commonly used traditional preparation *Baoji Pills*, as well as with a placebo, for patients with CCSDS. In this study, the investigators hypothesize that the duration of all symptoms will be shorter in the new tablets group. Additionally, it is expected that the new drug will be safe for oral administration.

## Methods/design

### Design

This study is designed as a multicenter, phase II, parallel-group, double-blind, double-dummy, randomized and placebo-controlled trial. The trial protocol is conducted in accordance with the Good Clinical Practice Guidelines and the Declaration of Helsinki (2008) [12]. This study has been authorized by the CFDA (Approval No. 2009L00225) and ethics approval has been obtained from local ethics committees, including the West China Hospital of Sichuan University Clinical Trials and Biomedical Ethics Committee, the Ethics Committee of the Affiliated Hospital of Jiangxi College of TCM, the Clinical Research Ethics Committee of Fujian Institute of TCM and the Ethics Committee of Guangxi Traditional Chinese Medical University. In addition, the study is registered with the Chinese Clinical Trial Registry (ChiCTR-TRC-13003197). The study is financially supported by Wanglaoji Pharmaceutical Co Ltd, Guangzhou, China. This funding source had no role in the design of this study and does not have any responsibility for analyses, interpretation of the data or the decision to submit results, other than providing test drugs. Trained research nurses introduce the trial to patients, and give them information sheets and consent forms. All patients have to give their written informed consent prior to enrollment. The study’s flow chart is shown in Figure 1.

**Figure 1 F1:**
[figure not shown]
Study flow chart.

### Patient population and setting

A total of 288 Chinese patients, who fulfill the screening criteria, will be enrolled at four large comprehensive hospitals in China: 1) West China Hospital of Sichuan University, 2) the Affiliated Hospital of Jiangxi College of TCM, 3) Fujian Institute of TCM and 4) Ruikang Hospital of Guangxi Traditional Chinese Medical University. Each center will recruit the same number of patients. In other words, 72 patients will be recruited at each hospital. A research assistant in each center will recruit patients through advertisements in local hospitals.

### Western medicine diagnostic criteria for the common cold

First, patients have to answer ‘yes’ to either of the following questions: A) Do you think that you have a cold? B) Do you think you are coming down with a cold? Second, patients have to report at least one of following four symptoms established previously as Jackson’s criteria [13]: 1) nasal discharge, 2) nasal obstruction, 3) sneezing and/or 4) a sore throat.

### Diagnostic criteria for TCM syndrome differentiation

The TCM diagnosis of summer-heat and dampness syndrome is based on the *Guidelines for Clinical Research of New Chinese Medicine*[14]. For a patient to be diagnosed with summer-heat and dampness syndrome, he/she will have at least two of each of the primary and secondary symptoms listed in Table 2, as well as the TCM signs for the tongue and pulse.

**Table 2 T2:** Traditional Chinese medicine diagnostic criteria

**Category**	**Symptoms and signs**
Primary symptoms	Aversion to cold, fever, diarrhea, nausea and vomiting
Secondary symptoms	Fatigue, headache, abdominal discomfort, poor appetite, belching
TCM signs for the tongue	Reddish tongue, greasy tongue coating
TCM signs for the pulse	Floating pulse, soft and slippery pulse

### Inclusion criteria

• Diagnosis of common cold according to Western medicine

• Diagnosis of summer-heat and dampness syndrome according to TCM

• Aged between 18 and 65 years old

• Presents within 48 hours after onset of common cold-like symptoms

• Able to understand and sign written informed consent

### Exclusion criteria

• Patients with acute herpetic pharyngitis, acute viral pharyngitis, acute herpetic laryngitis, acute viral laryngitis, acute conjunctivitis or acute tonsillitis

• Patients with acute bacterial gastroenteritis

• Patients with serious primary diseases of the heart, liver, kidney, blood system or endocrine system

• Patients with acute lower respiratory diseases, tumors or AIDS

• Patients with alanine aminotransferase levels 1.5 times higher than the upper limit of normal reference values, abnormal blood creatinine, positive urine protein qualitative test, blood leukocyte count < 3.0 × 10^9^/L or > 10.0 × 10^9^/L, neutrophil percentage > 80% or stool routine test using a high power objective finds white blood cell count > 1, pus cells or phagocytes

• Patient’s body temperature > 38.5°C

• Patients taking any medication before the study for relief of symptoms

• Pregnant women, hoping to become pregnant women, lactating women

• Patients who have an allergic constitution or are allergic to the trial medicine

• Mentally or legally disabled patients

• Patients who are participating or participated in another drug clinical trial within the prior 3 months

### Other criteria

Participants who meet any of the following criteria are withdrawn from the study:

• Voluntarily quitting

• Misdiagnosis

• Using forbidden drugs or treatments in the course of the trial

• Patient’s actual usage of trial drug is < 80% or > 120% of the required dosage

• Unable to complete the scheduled follow-up

• The patient’s condition worsens during the study and they need hospital treatment

• The patient cannot complete the study due to adverse events or other reasons

Patients who are withdrawn are not replaced.

The whole study will be terminated or suspended early if any of the following occur:

• Serious adverse event

• Poor curative effect is found during the study

• Significant deviation from the protocol

• Flawed protocol

• The pharmaceutical supervisory and administrative department decides to terminate the study for any reason

• The sponsors decide to terminate the trial due to management or funding problems

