### Concomitant treatments and forbidden drugs

Use of any other Western therapy or Chinese medicine to relieve symptoms, which may affect the analysis of the final results, is strictly prohibited. Medications used to control other conditions of the participants, such as hypertensive or diabetic medications, are allowed. The dosage, duration and name of any concomitant treatment or medication must be recorded carefully in the case report form (CRF).

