### Sample size calculation and statistical analysis

The sample size was determined using PEMS 3.1 with 90% power and alpha = 0.05 (two-sided). The mean duration of all symptoms for a common cold was estimated to be 7 days with a standard deviation of 4 days [15]. To demonstrate a reduction in the duration of all symptoms by 2 days, which is defined as clinically relevant, the sample size needs to be 85 cases for each group. Considering the potential loss of patients, the number of participants recruited must be 96 per group. Therefore, a total of 288 patients will be recruited in this trial.

The statistical analysis for this study will be performed by an independent professional statistician using PEMS 3.1 in a separate location. An intent-to-treat analysis for the patients, who have received treatment at least once, will be carried out. Missing data will be adjusted using the last observation carried forward method. The per-protocol analysis will be restricted to participants who strictly follow the protocol and complete the study. The safety analysis will be conducted only for randomized subjects who have completed at least one study visit. Pearson’s chi-square test or Fisher’s exact test will be performed on categorical variables, Student’s *t*-test on continuous normally distributed variables and the Wilcoxon rank sum test on non-normal variables. Due to the multicenter design, the Cochran–Mantel–Haenszel test stratified by clinical centers and analysis of covariance adjusted for clinical center and baseline will be used in this study. The statistical significance level will be set at *P* < 0.05 and 95% confidence interval will be calculated.

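### Patients are withdrawn from the study itself for forbidden medication, dosage or hospital treatment, so those still ill at withdrawal may have no recovery time for the promised intent-to-treat analysis

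*Protocol article*

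**What the plan says.** Under Other criteria, the protocol article states: "Participants who meet any of the following criteria are withdrawn from the study". The list includes "Using forbidden drugs or treatments in the course of the trial", "actual usage of trial drug is < 80% or > 120% of the required dosage", and the case where the patient's "condition worsens during the study and they need hospital treatment". It also covers voluntary quitting, misdiagnosis, missed follow-up and being unable to finish because of adverse events or other reasons. The section adds: "Patients who are withdrawn are not replaced".

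The section Concomitant treatments and forbidden drugs makes the scope of the forbidden treatments wide: "Use of any other Western therapy or Chinese medicine to relieve symptoms, which may affect the analysis of the final results, is strictly prohibited".

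Under Sample size calculation and statistical analysis: "An intent-to-treat analysis for the patients, who have received treatment at least once, will be carried out". The same paragraph says: "Missing data will be adjusted using the last observation carried forward method". It separately defines a per-protocol set of patients who kept strictly to the protocol and completed the study.

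Under Primary outcomes, the endpoint is the number of hours from baseline until the patient no longer feels ill, taken from the patient's diary. Under Interventions, the visits after baseline are at day 4 and day 11. No section says whether the diary or these visits continue after withdrawal.

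**The concern.** Adherence and forbidden-medication rules normally decide who enters the per-protocol set. Here they end participation in the study. An intent-to-treat analysis needs the outcome of each patient whatever happened after randomisation, and the withdrawal rule as written works against collecting it.

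The patients affected are not a random subset. Someone who takes another remedy for symptoms, or who needs hospital treatment, is likely to be recovering slowly. If the study drug works, such patients should be more frequent on placebo. Their long durations would then be missing, or replaced by something shorter, and the placebo arm would look better than it was. Withdrawals for adverse events could be unbalanced in either direction. In both cases the primary comparison stops being one between the groups as randomised.

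**Working it through.** **1. The plan's own figure.** Inputs from the sample-size section: SD 4 days, difference 2 days, two-sided alpha 0.05, power 90%.

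n per group = 2 × (1.960 + 1.282)² × (4/2)² = 2 × 10.51 × 4 = 84.1, rounded up to 85. The stated 85 is reproduced. Recruiting 96 per group (3 × 96 = 288) implies an allowance for loss of 1 − 85/96 = 11.5%.

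**2. Is power the problem?** Nominal power for a 2-day difference, by the share of the 96 per group whose outcome is lost (the loss rates are assumed):

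| Lost | Observed per group | Power |
|---|---|---|
| 0% | 96 | 93.4% |
| 11.5% | 85 | 90.3% |
| 20% | 76.8 | 87.3% |
| 30% | 67.2 | 82.6% |

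Power falls slowly. The problem is which patients are lost, more than how many.

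**3. Does withdrawal come before the endpoint?** Take the planning mean of 7 days and SD of 4, assume a normal shape, and count the duration from baseline. The share still ill at day 4 is 1 − Φ((4 − 7)/4) = Φ(0.75) = 77%. A withdrawal during the 3 days of treatment would therefore usually precede recovery.

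**4. Can LOCF fill the gap?** A symptom score has at least a baseline value that can be carried forward. The duration is measured once, at recovery, so a patient who is still ill has no earlier value of it. If the time to the last diary entry were used instead, a patient still ill would be counted as recovered on the day of withdrawal.

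**5. How large could the bias be?** Let a fraction w of an arm be withdrawn, and let those patients be ill g days longer on average than those who stay. If the arm's overall mean is M, the mean of those who stay is M − w·g. With the same M in both arms, the shift in the observed difference (active minus placebo) is (w_placebo − w_active) × g. The documents give neither w nor g, so all values here are assumed.

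- 5% vs 15%: 0.10 × 2 = 0.2 days; 0.10 × 4 = 0.4 days.
- 5% vs 20%: 0.15 × 2 = 0.3 days; 0.15 × 4 = 0.6 days.

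In this scenario the shift favours placebo: a true 2-day reduction would appear as 1.8 to 1.4 days. If the active arm lost more patients, the sign would reverse.

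**6. The dosage rule.** Three doses a day for 3 days make 9 doses. One missed dose leaves 8/9 = 89%. Two leave 7/9 = 78%, below 80%, which triggers withdrawal.

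**The case against.** The strongest reply is that loss of outcomes is inferred. The article does not say that the diary stops or that data are discarded. It keeps every treated patient nominally in the intent-to-treat analysis, and a full protocol that is not shown may provide for later data collection. This stands as a limit on the wording: the affected patients would be imputed, not excluded, and the loss is implied, not declared. It does not remove the point, because the only rule stated takes patients out of the study, and an analysis plan cannot recover data that sites have stopped collecting.

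A reader might also infer that the 80% rule removes fast recoverers from the intent-to-treat comparison. Under the planning figures, 3.6-12.2% of patients with a mean of 7 days, and 12.1-28.7% with a mean of 5 days, would recover within 2.33 days, the time of seven doses. The documents do not support that reading. A patient who recovers and then stops the drug already has a recovery time in the diary, so these percentages do not measure lost outcomes. They are upper bounds on exclusion from the per-protocol set, and assume that every early recoverer stops.

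Three further limits stand:

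- No visit is scheduled between baseline and day 4, and usage would naturally be checked when packages are reclaimed. Low dosage would thus mostly be found at or after the day-4 visit, so many day-4 scores would exist.
- Misdiagnosis is a fact about eligibility at baseline, and under blinding it should not depend on arm.
- The worsening criterion requires hospital treatment, which should be uncommon in an illness that the Background calls mild and self-limited.

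What remains is the patient withdrawn while still ill, mainly for forbidden symptom relief.

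**Conclusion.** The concern holds in this form: the withdrawal rule and the intent-to-treat statement do not fit together for patients who leave the study before recovery. Their primary outcome would be unobserved and LOCF cannot supply it. Since these withdrawals can depend on arm and prognosis, the primary comparison can be biased.

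The documents do not fix the size. The 0.2-0.6 days rests entirely on assumed withdrawal rates and an assumed excess duration, and should be read as an illustration. It does not show that the randomised comparison is lost altogether. For early recoverers who stop the drug, the effect falls mainly on the per-protocol set. The conclusion also assumes that withdrawal from the study means what it says and that no unseen text keeps follow-up going.

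**What to change.** Reconcile the withdrawal list with the intent-to-treat statement, changing only data collection and analysis sets:

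- Separate stopping study drug from leaving follow-up. State that the diary and the day-4 and day-11 visits continue for every randomised patient unless consent to data collection is withdrawn.
- In the intent-to-treat analysis, use the observed recovery time whatever the adherence or other medication.
- Apply the forbidden-treatment and 80-120% criteria only to define the per-protocol set, at the blind review already planned under Data management.

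The clinical criteria for stopping treatment are not touched. Voluntary quitting, hospital treatment and adverse events should not be relabelled as protocol deviations.

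The planned sample size does not change. With all 96 per group observed, nominal power is 93.4%, before any dilution from non-adherence or other remedies. The cost is a change of wording plus follow-up of the few patients who would otherwise have been dropped, on visits and a diary that already exist. The article reports that the trial is recruiting, so the change is worth making soon: outcomes not collected after a withdrawal may not be recoverable.

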### Concomitant treatments and forbidden drugs

Use of any other Western therapy or Chinese medicine to relieve symptoms, which may affect the analysis of the final results, is strictly prohibited. Medications used to control other conditions of the participants, such as hypertensive or diabetic medications, are allowed. The dosage, duration and name of any concomitant treatment or medication must be recorded carefully in the case report form (CRF).

### Test drugs

The test drugs are *Baoji Tablets*, dummy *Baoji Tablets*, *Baoji Pills* and dummy *Baoji Pills* and they are manufactured by Wanglaoji Pharmaceutical Co Ltd. Dummy drugs are indistinguishable from the real ones. They are almost the same in shape, size, taste and color. To make blinding more effective, both dummy and real drugs use the same packaging. A uniform test drug package contains both tablets and pills for 3 + 1 days’ dosage. A clearly visible tag on each package states: ‘FOR TRIAL USE ONLY’ and other information, such as the manufacturer’s name, drug name, drug code, usage, dosage and so on. All test drug packages are dispensed and reclaimed by an independent drug administrator in each center, who is also responsible for storing and keeping records of test drugs.

